6.1. Statistical methods to be used [28](#__RefHeading___Toc246224633)

6.2. Efficacy evaluation: [28](#__RefHeading___Toc246224634)

6.3. Safety assessment [28](#__RefHeading___Toc246224635)

6.4. Number of subjects [28](#__RefHeading___Toc246224636)

6.5. Primary endpoint analysis [28](#__RefHeading___Toc246224637)

6. 6. Rules for discontinuation [29](#__RefHeading___Toc246224638)

Summary of Protocol

1. **Background**

The principal morbidity following axillary node dissection within the scope of breast cancer surgery is the post-operative development of lymphocele. According to the literature, incidence can vary from 4 to 89% depending on the type of surgery, whether or not a drain is inserted or a compression dressing applied and the time at which the drain is removed… In our experience, the incidence is 40% [IGR (Gustave Roussy Institute) data focusing on 70 patients between November 2008 and February 2009].

Encouraging results in terms of reducing postoperative lymphoceles as well as drainage duration and volume using Octreotide have been recorded in two recent studies. A new molecule developed by Novartis Laboratories, namely pasireotide, is a somatostatin analog possessing strong affinity for several somatostatin receptors (30 to 40 times greater for sst1 and sst5, 5 times greater for sst3 and equivalent for sst2)

1. **Purpose**

The purpose of this trial is to assess the efficacy of a pre-surgical injection of pasireotide LAR in reducing the postoperative incidence of symptomatic lymphoceles following axillary node dissection.

The secondary objectives are to assess the efficacy of prolonged release pasireotide on the duration of postoperative drainage, the daily drainage volume, the total drainage volume, the number of repeated lymphocele aspirations and the volume, the total volume of lymph aspirated, the incidence of postoperative febrile episodes, the length of hospital stay, and the length of time to onset of adjuvant chemotherapy. It is also to assess the safety of prolonged release pasireotide.

1. **Trial design**

We recommend a prospective, randomized, two-center trial according to a Bayesian design with a control arm receiving a placebo.

1. **Trial population**

All female patients for whom mastectomy - axillary node dissection is indicated at the pre-surgical stage will be eligible for inclusion. Control population of an identical size: randomization 1:1.

1. **Study Procedure**

- Inclusion criteria: any female patient scheduled for breast surgery with mastectomy and axillary node dissection indicated at the pre-surgical stage.

- Exclusion criteria:

- Female patient under the age of 18 or

- Patient unable to understand French

- Patient must be affiliated to the French National Health Insurance System

- Refusal by the patient

- Scheduled sentinel node procedure

- Patient exhibiting one or more contraindications to anesthesia and surgery

- Pasireotide administration contra-indicated: abnormal coagulation

- Women able to conceive and not practising an effective method of birth control

- Pregnant or breast-feeding women

- Poorly controlled diabetes (HbA1c > 8%)

- History of radiotherapy

- Recurrent breast cancer

- Patient with a congestive cardiac insufficiency (NYHA category III or IV), an instable angina pectoris, sustained ventricular tachycardia or ventricular fibrillation episodes or history of myocardial infarction during the last 6 months.

- Patient presenting an extension of QT interval (QT corrected according to the Fridericia formula (QTcF)) at the screening or baseline (predose) > 450msec

- History of syncope or family history of sudden death or significant cardiac arrhythmia

- Risk factors for torsades de pointes: hypokaliaemia, hypomagnesaemia, known structural or ischaemic cardiac disease, bradycardia (HR<55/min) or high grade AV block

- Concomitant disease that could prolong QT or increase exposure to the study medication including dehydration, renal or hepatic impairment

- Concomitant medication known to increase the QT interval

- Patient with an hepatic pathology such as cirrhosis, chronic hepatitis active or persistent, or an elevation of ALAT rate, ASAT rate twice higher than the normal superior limit (NSL)

- Patient having leucocytes < 3x109/L, Hb < 90% LIN, platelets < 100x109/L

- Patient having a pathology or medical history susceptible to interfere with the realization of the study or results evaluation according to the judgment of the investigator or the study monitor

- Patient participating to another clinical trial with another molecule in study during the month before the first dose

- Known oversensitivity to somatostatine analogs or another component of prolonged release pasireotide or prolonged release octreotide formulations.

- **Inclusion and signature of the informed consent form prior to surgery.**

- 1 intramuscular injection of prolonged-release pasiretotide or placebo 7 to 10 days before surgery

- Collection of surgical and post-surgical data (onset of a lymphocele, need for aspiration, number and volume of each repeated aspiration, daily drainage volume, duration of drainage, local infectious complications or delayed healing).

1. **Primary and secondary endpoints**

-The primary endpoint of this study is the patient ratio who did not have post-operative axillary symptomatic lymphoceles defined as the absence of aspiration or a unique or iterative aspirations global volume of lymphoceles inferior to 60cc inclusive (≤) in the 28 days after the intervention or a systematic aspiration volume at the 28th day inferior to 120cc inclusive (≤).

- Secondary endpoints: total quantity of lymph drained on D5 and up to removal of drains, duration of drainage, daily drainage volume, aspirated volumes of lymph in the case of aspiration, local healing, infections, fever, length of hospital stay, length of time to onset of adjuvant chemotherapy.

1. **Statistical analysis and trial design**

The statistical analysis will be carried out sequentially after observing the principal criterion (i.e. success is defined as a total volume of lymphocele following single or repeated aspiration ≤ 60 cc in the 28 days following surgery or a routine aspiration volume on the 28th day ≤ 120cc) of each patient included for each randomization group, with or without treatment.

It involves estimating the probability of a response in each group (proportion of patients who will not have undergone lymphocele aspiration or the aspiration of a total volume of ≤ 60cc or ≤ 120cc for the aspiration carried out on the 28th day after surgery) using a Bayesian design based on a beta-binomial model. With the Bayesian approach, the response rate in each group (*i*) is considered as a random variable, with *a priori* density focused on the anticipated response rate of 80% in the group receiving treatment and 60% in the non-treatment group, which will be sequentially updated as the observations are made according to a so-called *a posteriori* law.

A total of 90 patients will be included over 12 months with 45 patients in the treatment group and 45 patients in the non-treatment group.

# 1. Introduction

Octreotide, a somatostatin analog, has demonstrated its efficacy in the medical management of postoperative gastro-intestinal and pancreatic fistulae. Two recent studies have shown its value in reducing lymphoceles following axillary node dissection performed as part of breast cancer surgery.

The principal morbidity following axillary node dissection within the scope of breast cancer surgery is the postoperative development of lymphocele following the removal of an axillary drain. This may be a source of pain, repeated aspiration, infection and delayed local healing.

Pasireotide, a somatostatin analog under evaluation and possessing a high affinity for somatostatine receptors (30 to 40 times greater for sst1 and sst5 receptors, 5 times greater for sst3 and equivalent for sst2) is an attractive molecule in this indication.

Based on the encouraging results published with octreotide and the greater effects anticipated with pasireotide, we want to assess the benefit of preoperative administration of pasireotide in reducing the incidence of axillary lymphoceles following mastectomy - axillary node dissection.

## 1.1. Mode of action of pasireotide

Somatostatin is a hormone that is widely distributed in the nervous and gastropancreatic system responsible for a variety of pharmacological and physiological effects. It can inhibit gastrointestinal endocrine and exocrine secretion and has an anti-inflammatory action (1). The direct effect of somatostatin on lymphatic flow has only been observed on the gastrointestinal tract.

Several series report the use of octreotide in the treatment of chylous ascites or in the management of thoracic duct injury (2). Although its mechanism of action has not been studied in depth, it probably acts by inhibiting splanchnic blood flow and limiting the absorption of triglycerides.

Somatostatin receptors have been demonstrated in lymphatic tissues, including those not associated with the intestinal tract. It is therefore probable that the inhibitory action of somatostatin on gastrointestinal lymphatic flow may also apply elsewhere in the body, and to the lymphatic system in particular.

Somatostatin might therefore decrease lymphatic flow following essentially axillary lymphadenectomy.

A new molecule, pasireotide, is currently in clinical development. This molecule is a somatostatin analog possessing an affinity 30 to 40 times greater for sst1 and sst5 receptors, 5 times greater for sst3 and comparable for sst2 than octreotide. It could therefore have a greater effect than octreotide.

The gradual release form must be injected intramuscularly prior to surgery. An effective plateau concentration is obtained after 10 days regardless of the selected dosage (20, 40, or 60 mg) (3).

## 1.2 Literature review

In addition to the many articles in the literature detailing the beneficial effects of octreotide on gastrointestinal and pancreatic fistulae and on regression of chylous ascites and chylothorax, a few articles have attempted to highlight its effect on postoperative lymphoceles.

Firstly, two articles have highlighted the positive effect of somatostatin analogs in reducing drainage volume and the incidence of lymphoceles following axillary node dissection in breast cancer:

- In 2003 Carcoforo et al. (4) revealed a significant difference between a group of patients treated with subcutaneous octreotide during the immediate postoperative period and an untreated group. The treated group had smaller drainage volumes (65.4 vs. 94.6 ml, p=0.0001) and their drains were removed sooner after surgery (7.1 vs. 16.7 days, p=0.0001).
- Another more recent article by Mahmoud et al. (5) showed the same beneficial effects on the mean daily drainage volume (104 vs 145 ml, p=0.0001), the total duration of drainage (12.7 vs 25 days, p=0.0001) and the need for postoperative aspiration of lymphoceles (90 vs 40%, p=0.0001).

In 2006, in a different field (that of renal transplantation), an article by Capocasale et al. (6) showed that lymphatic leakage following transplantation was of shorter duration in the octreotide-treated group. Furthermore, a lower incidence of lymphocele was observed after drain removal.

Pasireotide is an injectable somatostatin analog. Like natural somatostatin and known analogs, its pharmaceutical efficacy depends on its binding to somatostatin receptors. There are five of these (sst 1 to 5); they are expressed in various bodily tissues under normal physiological conditions. Somatostatin analogs activate these receptors, which in turn reduce cell activity and inhibits hormone synthesis. (7). Octreotide and lanreotide, which are currently used, have a strong affinity for the sst2 receptor and moderate affinity, if any, for the other types. Pasireotide possesses greater affinity than octreotide for certain somatostatin receptors: 30 times greater for sst1, 5 times greater for sst3 and 40 times greater for sst5. It possesses equivalent affinity for sst2 and none (like octreotide) for sst4. (8)

The side effects described with pasireotide include potential transient, post-prandial, dose-dependent hyperglycemia, which mainly appears as from the administration of injections of 600g. Intestinal disorders have been reported (diarrhoea, nausea and vomiting) but do not generally warrant medication since they spontaneously disappear as treatment continues.

In the literature, the incidence of axillary lymphoceles following surgery for breast cancer varies considerably: a recent meta-analysis of 66 studies revealed an incidence of 4 to 89 % depending on whether or not drainage was being carried out, the type of surgery (conservative or not), the time at which the drain was removed and whether or not a compression dressing was applied.

In our experience, the incidence at Hôpital Tenon is 40%. This percentage has been corroborated by Gustave Roussy Institute data, which recorded an incidence of 39.3% in out of 70 patients who underwent surgery between November 2008 and February 2009.

## 1.3 Somatostatin analogs and cancer

# Several teams have reported their use of Sandostatin® or other somatostatin analogs in the management of patients suffering from inoperable peritoneal carcinoma (9-12). This treatment was used as supportive therapy and reduced the incidence of symptoms associated with an obstructive syndrome. It fact, it can reduce gastrointestinal secretions. Some authors have even suggested that somatostatin analogs possess an anti-tumor effect (9). Octreotide is recommended by AFSSAPS in the treatment of palliative care patients presenting with intestinal occlusion in peritoneal carcinoma. Since a Marketing Authorization (MA) has been granted for the use of somatostatin analogs in patients presenting with a gastrointestinal endocrine tumor, the use of pasireotide does not raise any specific ethical issue (13).

# 2- Study objectives

## 2.1 Primary objective

The primary objective of this study is to assess the efficacy of a preoperative prolonged release pasireotide injection in the reduction in the incidence of symptomatic, postoperative axillary lymphoceles following mastectomy-axillary node dissection.

## 2.2 Secondary objectives

The secondary objectives of this study are:

- to evaluate the efficacy of prolonged release pasireotide on:

- the duration of postoperative drainage
- the daily drainage volume
- the total drainage volume
- the number of repeated lymphocele aspirations and the volume.
- the total volume of lymph aspirated
- the incidence of postoperative febrile episodes
- the length of the hospital stay
- the length of time to onset of adjuvant chemotherapy

- to evaluate the safety of prolonged release pasireotide

# 3. Study protocol

## 3.1. Global study design

### 3.1.1. Type of trial

Randomized, multicenter, prospective, Bayesian trial with a control group.

Since the control group receives a placebo injection, it can be used to validate the incidence of lymphocele following mastectomy and axillary node dissection during the study period (the incidence varies considerably according to the literature). It can be used to calculate the study number if a decision is taken to carry out a phase III study.

### 3.1.2. Study design

- The Ji data correspond to the length of time compared to the injection of pasireotide or placebo [J1 = day of injection], Ki data correspond to the duration of the procedure [K0=day on which surgery is performed].
- Screening: reporting and presurgical visit
  - Check for compliance with inclusion and non-inclusion criteria
  - Explanation of the trial to the patients
  - Issue of the Patient Information Letter
- Baseline visit (V1 = J1) 7 to10 days before surgery (K-10 to K-7):
  - Consent form signed
  - Injection of pasireotide or placebo by a consultation nurse who will not be present during subsequent visits since aspiration may be required.
  - Recording of adverse events
  - Blood sample for pharmacokinetic monitoring
  - ECG
- Visit V2 (day of surgery or day after surgery [K0 or K1]): collection of data concerning the operation (type of surgery, duration, intraoperative complications, type and number of drains)
  - Recording of adverse events:
- Visit V3 (day of discharge: K4 to K7 post-surgery): Summary of the daily collection of postoperative data:
  - The daily and total drainage volumes
  - Date on which drains were removed and overall duration of drainage
  - Postoperative complications (hematoma, skin necrosis, etc.)
  - Whether aspiration of a symptomatic lymphocele was required
  - Length of hospital stay
  - Recording of adverse events:
- Immediate postoperative visit (V4): 14+/- 2 days following surgery (K12 to K16)
  - The number of repeated lymphocele aspirations and the volume (patients requiring an aspiration will be seen during the interval between two consultations at the hospital and data will be colligated in the medical file. To ensure the lymphoceles sufficiency, a free phone number will be given to the patient in order that she could report any event if necessary.)
  - Recording of adverse events
  - ECG
  - Blood sample for pharmacokinetic monitoring
- Postoperative visit (V5): 28+/- 4 days following surgery (K24 to K32)
  - Routine lymphocele aspiration is considered positive if the volume aspirated exceeds 120cc.
  - The number of repeated lymphocele aspirations and the volume (patients requiring an aspiration will be seen during the interval between two consultations at the hospital and data will be colligated in the medical file.
  - Adjuvant chemotherapy start date, if required
  - Recording of adverse events
- Follow-up visits at two months (V6)
  - Recording of adverse events

**Figure 1: Trial design**

14 d

**Screening**: trial explanation

**V1**: Baseline visit

Signature of consent

Randomization

**Surgery:** Axillary node dissection

**V4**

**V5**

28 d

7 to 10 d

**V =** visit

**Injection of pasireotide or placebo**

**V2**

**V3**

**V6**

2 months

## 3.2. Discussion of the type of study

We want to assess the efficacy of prolonged release pasireotide because its safety has already been demonstrated and is well known (13). A phase 3 study is irrelevant in the absence of numerical efficacy data. The incidence of symptomatic lymphocele aspiration following mastectomy - axillary node dissection varies according to the literature and although our initial experience suggests an incidence rate of 40%, a control group is required. This is why we recommend a randomized phase II study.

## 3.3. Study population

### 3.3.1. Patient population

All female patients for whom mastectomy - axillary node dissection is indicated at the pre-surgical stage will be eligible for inclusion including patients who have received neo-adjuvant chemotherapy.

### 3.3.2. Inclusion and non-inclusion criteria

**Inclusion Criteria:**

- Female patient aged 18 years or over.
- Patient understands French.
- Patient covered by the French national health insurance system.
- Any female patient scheduled for breast surgery with mastectomy and axillary node dissection indicated at the pre-surgical stage.

**Non-inclusion Criteria:**

- Patient under the age of 18 years.
- Patient who does not understand French.
- Patient not covered by the French national health insurance system.
- Patient exhibiting one or more contraindications to anesthesia and surgery.
- Patient with a contra-indication to pasireotide
- Refusal by the patient
- Scheduled sentinel node procedure
- Abnormal coagulation or curative anticoagulant treatment
- Women of child-bearing potential without effective contraception,
- Pregnant or breast-feeding women
- Poorly controlled diabetes (HbA1c > 8%)
- History of radiotherapy
- Recurrent breast cancer
- Patient with a congestive cardiac insufficiency (NYHA category III or IV), an instable angina pectoris, sustained ventricular tachycardia or ventricular fibrillation episodes or history of myocardial infarction during the last 6 months.
- Patient presenting an extension of QT interval (QT corrected according to the Fridericia formula (QTcF)) at the screening or baseline (predose) > 450msec
- History of syncope or family history of sudden death or significant cardiac arrhythmia
- Risk factors for torsades de pointes: hypokaliaemia, hypomagnesaemia, known structural or ischaemic cardiac disease, bradycardia (HR<55/min) or high grade AV block
- Concomitant disease that could prolong QT or increase exposure to the study medication including dehydration, renal or hepatic impairment
- Concomitant medication known to increase the QT interval
- Patient with an hepatic pathology such as cirrhosis, chronic hepatitis active or persistent, or an elevation of ALAT rate, ASAT rate twice higher than the normal superior limit (NSL)
- Patient having leucocytes < 3x109/L, Hb < 90% LIN, platelets < 100x109/L
- Patient having a pathology or medical history susceptible to interfere with the realization of the study or results evaluation according to the judgment of the investigator or the study monitor
- Patient participating to another clinical trial with another molecule in study during the month before the first dose
- Known oversensitivity to somatostatine analogs or another component of prolonged release pasireotide or prolonged release octreotide formulations.

### 3.3.3. Interruption or discontinuation of treatment

The date and reason for withdrawal from the study or early treatment discontinuation must be entered in the Case Report Form. The investigators must make every effort to ensure that patients continue to participate and take the study medication throughout the trial. A final evaluation will be carried out and documented in the corresponding section of the Case Report Form (visit and study completion page) in the event of withdrawal from the study or early treatment discontinuation.

Patients may be withdrawn from the study for one of the following reasons:

- adverse, intolerable event(s),
- protocol violation, appearance of a protocol non-inclusion criterion,
- withdrawal of consent,
- patient lost to follow-up,
- administrative problem,
- death,

Any patient who withdraws from the study due to an adverse event or laboratory abnormality must be followed up until this adverse event has been resolved or the laboratory abnormality has returned to normal. Patients who are early withdrawn from the study will not be replaced.

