### 3.4.5. Treatment compliance

Since treatment comprises a single injection adminstered at the hospital by a state registered nurse, there are no treatment compliance issues.

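### Section 3.3.3 lets patients be withdrawn from the study after the only injection without requiring the day-28 outcome, so primary outcomes may be lost, possibly unequally between arms

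*Protocol*

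**What the plan says.** Section 3.3.3 introduces its list with "Patients may be withdrawn from the study for one of the following reasons". The list contains intolerable adverse events, "protocol violation, appearance of a protocol non-inclusion criterion", withdrawal of consent, loss to follow-up, administrative problems and death. The same section asks investigators to make every effort to keep patients in the trial and on study medication. It requires a final evaluation at any withdrawal, and says that a patient who leaves because of an adverse event or laboratory abnormality "must be followed up until this adverse event has been resolved" or the laboratory value is back to normal. It adds: "Patients who are early withdrawn from the study will not be replaced".

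Sections 3.4.2 and 3.4.5 fix treatment as one intramuscular injection, given 7 to 10 days before surgery. Section 3.4.5 draws the consequence itself: "Since treatment comprises a single injection adminstered at the hospital by a state registered nurse, there are no treatment compliance issues".

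The primary endpoint (section 3.5.3.1) rests on aspiration volumes over the 28 days after surgery and on a routine aspiration at day 28, which is done at V5.

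**The concern.** Section 3.3.3 reads as if written for a trial with continuing medication, where leaving treatment and leaving the study are easily run together. Here the last dose is also the first. After V1 the investigator can withdraw the patient only from observation, and the observation at risk is the primary endpoint.

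Three of the listed reasons do not by themselves prevent a patient from being followed: an adverse event, a protocol violation, and a non-inclusion criterion that appears later. Each can arise after randomisation, and at least the first can be related to treatment. Removing such patients before their outcome is known gives up part of the protection of randomisation, in a trial of 45 per arm without replacement. An analysis plan can say how missing outcomes are counted. It cannot recover aspiration volumes that the protocol never asked anyone to collect.

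**Working it through.** **1. Time at risk.** The injection is given 7 to 10 days before surgery and V5 falls 24 to 32 days after it. The interval from injection to the routine aspiration is therefore 7 + 24 = 31 days to 10 + 32 = 42 days. A withdrawal at any point in that interval can cost the primary outcome.

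**2. Do the existing safeguards secure the outcome?**
- Final evaluation: required, but neither its content nor its timing relative to day 28 is stated.
- Adverse-event follow-up: ends when the event resolves, and is tied neither to day 28 nor to aspiration volume.
- Retention instruction: helpful, but it stands beside reasons that let the investigator end participation.

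None of the three requires aspiration data to day 28.

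**3. What the protocol gives for sizing.** There is no expected withdrawal rate, and the 90 patients of section 6.4 come without a power calculation or target precision, so no stated figure can be reproduced. The numbers of lost outcomes below are assumptions.

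**4. Effect on the observed rate.** Take one arm of n = 45 (section 6.4) with a true result of 36 successes, which is the anticipated 80% (section 6.5). Let k outcomes be lost and those patients left out of the estimate. The upper bound is 36/(45 − k), if every lost patient was a failure. The lower bound is (36 − k)/(45 − k), if every lost patient was a success.

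**5. Effect on criterion 2.** Section 6.6 concludes efficacy when the posterior probability that the rate exceeds 80% is above 0.90. With the beta-binomial model of section 6.5, this is P(p > 0.80) for p ~ Beta(0.8w + r, 0.2w + m − r), where r successes are seen in m patients. The prior mean is set at 0.80. The prior weight is not given, so w = 1, 2 and 5 patients are assumed; results differ by about 0.01 at most across these.

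| Lost, k | Lower bound | Upper bound | Criterion 2, lower to upper |
|---|---|---|---|
| 0 | 36/45 = 80.0% | 36/45 = 80.0% | 0.53 |
| 2 | 34/43 = 79.1% | 36/43 = 83.7% | 0.47 to 0.76 |
| 5 | 31/40 = 77.5% | 36/40 = 90.0% | 0.38 to 0.96 |
| 9 | 27/36 = 75.0% | 36/36 = 100% | 0.26 to 1.00 |

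**6. How extreme must the loss be?** With k = 5:
- all five failures (36/40): 0.956 to 0.965 over the three weights, above the limit;
- four of five failures (35/40 = 87.5%): 0.898 to 0.910, at the limit;
- three of five failures (34/40 = 85.0%): 0.80 to 0.82, below the limit;
- one of five failures, the same 80% success as the arm (32/40 = 80.0%): 0.53, unchanged.

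The bias depends on how strongly loss is related to outcome, and can go either way.

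**7. Is it a power problem?** No. As a reference only, a two-sided 0.05 comparison of 60% with 80% has power 54.5% with 45 v 45 and 51.5% with 45 v 40. The smaller numbers cost little; the issue is bias.

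**The case against.** The strongest reply is that section 3.3.3 is permissive, covers both arms and comes with an instruction to retain patients, while patients and surgeons are blinded under section 3.4.3. All of that stands.

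A reader might go further and infer that the rule removes outcomes selectively from the pasireotide arm. The protocol does not support this as a fact. Section 1.2 lists hyperglycaemia and intestinal disorders with pasireotide, but calls the former transient and says the latter generally disappear without medication. The route from those effects to a new non-inclusion criterion is weak. The diabetes criterion is an HbA1c above 8%, and the visit table schedules no HbA1c after injection. The QTcF limit applies at screening or before the dose. Protocol violations are not specific to an arm. What remains is that intolerable adverse events may be more frequent on active drug than on saline.

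A reader might also infer that the protocol contradicts itself on an early leaver, counting her a success because she had no aspiration and a non-response because she is among those included. The text does not plainly say either. The endpoint refers to the full 28 days, and section 6.5 analyses patients after the criterion has been observed. How to count an outcome that is still missing can be set in the analysis plan, and a rule that missing means failure is debatable.

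Nor does leaving the study always delete the outcome: the final evaluation may recover part of it. Finally, a patient who is never operated on has no V5, so follow-up to V5 cannot apply to her. None of this supplies the missing requirement to collect the day-28 outcome.

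**Conclusion.** The point holds as a badly fixed rule in the protocol: after a single injection, patients may be taken out of the study for reasons that do not prevent follow-up, with no requirement to collect the primary outcome. Unequal loss between arms is a risk, not an established effect.

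The size depends on assumptions: all losses in one arm, prior weights of 1 to 5 patients, and lost patients left out of the estimate. Two losses in 45 matter little for criterion 2, which stays below 0.90 even at the extreme. With five, the upper bound lies 10.0 points above the true rate (90.0 − 80.0), half of the 20-point difference anticipated, and the 0.90 limit can be crossed if four or five of the lost patients were failures. If loss is unrelated to outcome, the rate is not biased. The protocol does not say which case applies, and the correction is cheap enough that it should be made.

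**What to change.** Reword section 3.3.3 to separate the end of treatment from the end of follow-up:
- Record intolerable adverse events, protocol violations and newly appearing non-inclusion criteria, but remove them as reasons to end follow-up.
- Collect aspiration data to V5 and safety data to V6 in every randomised patient who is operated on, and continue safety follow-up in those who are not.
- Let follow-up end early only when consent is withdrawn, contact is lost or the patient dies.
- Delete the wording about taking study medication throughout the trial, which does not fit a single injection.

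The handling of outcomes that are still missing can be left to the analysis plan.

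Cost: an amendment to one section, and a few more completed visits by patients who would otherwise have left, all of them already in the visit schedule.
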